#### Secondary predictions

Patients receiving Motivational Care Planning are expected to have reduced readmission rates for injury, although the study may be insufficiently powered to detect this effect.

## Sample size

Assuming equality between conditions at Baseline, the study is powered to detect a differential reduction in alcohol consumption of 0.50 SD in weekly alcohol consumption [58]. We argue that this is the minimum difference of any clinical significance. Setting the power at 0.80 and alpha at 0.05, 62 participants are required in each condition. While data will be analysed by intention to treat, the sample size allows for 20% attrition, deriving a target baseline sample of 154.

## Analysis

Continuous outcome variables are assessed for normality prior to analysis and transformed if necessary. Primary analyses use Linear Mixed Models analyses comparing the 2 conditions (MCP vs TAU) over 2 occasions (Baseline, 3 and 6 months post-baseline), allowing the analysis of data on all participants allocated to conditions at Baseline (i.e. intention to treat).

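### The primary mixed model should constrain baseline means to be equal: on its natural reading it is close to a change-score analysis, which gives up precision and reaches the planned power only if an unstated correlation is about 0.5 or more

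*Protocol article*

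**What the plan says.** The Analysis section of the protocol article states: "Primary analyses use Linear Mixed Models analyses comparing the 2 conditions (MCP vs TAU) over 2 occasions". The bracket that follows names baseline, 3 months and 6 months, which is three times rather than two. Aims of the study and Follow up assessment give only baseline and 6 months. The section intends every allocated participant to contribute. It does not name the tested term, say whether baseline means are free or common to both conditions, or mention baseline as a covariate.

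The Sample size section states: "Assuming equality between conditions at Baseline, the study is powered to detect a differential reduction in alcohol consumption of 0.50 SD in weekly alcohol consumption". It continues: "Setting the power at 0.80 and alpha at 0.05, 62 participants are required in each condition", and adds that "the sample size allows for 20% attrition, deriving a target baseline sample of 154". It gives no correlation between baseline and follow-up and no SD of change.

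The primary predictions are framed as larger reductions under Motivational Care Planning (MCP) than under Treatment as Usual (TAU). The Procedure section places the full assessment before random allocation.

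**The concern.** When baseline is an outcome occasion and the hypothesis concerns differential reduction, the usual test is the condition-by-occasion interaction. If each condition has its own baseline mean, that interaction equals the difference in mean change when data are complete. Its variance then includes the chance baseline difference between the arms.

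The sample size calculation removes that difference by assumption ("Assuming equality between conditions at Baseline"), but nothing in the Analysis section carries the assumption into the model. The power statement and the analysis therefore agree only under a condition on r that is not stated. Whatever r is, short of 1, the free-baseline model also discards precision available from data collected before allocation.

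**Working it through.** **Inputs from the protocol article.** Effect 0.50 SD of weekly consumption, power 0.80, alpha 0.05, 62 per condition with follow-up, 154 at baseline (77 per condition), all from Sample size. Sidedness is not stated. Two-sided is inferred, because a one-sided test would need 50 per arm.

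**Assumptions, not in the document.** The correlation r (range shown), equal SDs at baseline and 6 months, and the 0.50 SD being on the scale of weekly consumption rather than of change.

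**1. The plan's own figure.** n per arm = 2(1.960 + 0.842)² / 0.50² = 62.8, so 63 (64 by the t distribution). The stated 62 agrees to within rounding, and power at 62 is 0.795 (normal approximation). For attrition, 124 / 0.8 = 155 against the stated 154. The calculation is therefore a plain two-sample comparison of means with no r in it.

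**2. Equivalence on complete data.** One simulated data set, 62 per arm, r = 0.3:

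| Analysis | Estimate | SE |
|---|---|---|
| Mixed model, free baseline means | -0.636 | 0.211 |
| Change score | -0.636 | 0.211 |
| Mixed model, common baseline mean | -0.674 | 0.160 |
| ANCOVA | -0.674 | 0.164 |

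**3. Variances for the planned data.** With unit SD, 77 baselines and 62 follow-ups per arm, the variance per arm is:

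- Free baseline means: (1 - r²)/62 + (1 - r)²/77
- Common baseline mean: (1 - r²)/62

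Power = Φ(0.50 / √(2 × variance per arm) - 1.960).

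Example at r = 0.3:

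- Free: 0.91/62 + 0.49/77 = 0.01468 + 0.00636 = 0.02104. Then 0.50/√0.04208 = 2.437, so power = Φ(0.477) = 0.683.
- Common: 0.01468. Then 0.50/√0.02935 = 2.918, so power = Φ(0.958) = 0.831.
- Variance reduction: 0.00636/0.02104 = 30%.

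| r | Power, free baseline | Power, common baseline | Variance reduction |
|---|---|---|---|
| 0.2 | 0.630 | 0.811 | 35% |
| 0.3 | 0.683 | 0.831 | 30% |
| 0.4 | 0.745 | 0.859 | 26% |
| 0.5 | 0.814 | 0.895 | 21% |
| 0.6 | 0.888 | 0.936 | 17% |

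The free-baseline model reaches 0.80 at about r = 0.48: 0.7696/62 + 0.2704/77 = 0.01593, and 0.50/√0.03185 = 2.80.

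**4. Complete pairs only (62 per arm).** The change-score SD is √(2(1 - r)) and the adjusted SD is √(1 - r²). Power is 0.653 against 0.831 at r = 0.3, 0.720 against 0.859 at r = 0.4, and 0.795 against 0.895 at r = 0.5. Simulation with 4,000 trials per r gave 0.64 against 0.82, 0.71 against 0.85, and 0.79 against 0.89. The baseline-only participants thus soften the loss by about 2 to 3 points at these values of r but do not remove it.

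**The case against.** The strongest objection is that free baseline means are an inference. The Analysis section names a mixed model and its occasions. A model with a common baseline mean also fits those words, and the equal-baseline assumption in Sample size is compatible with it. How baseline is parameterised is also commonly left to an analysis plan. This stands as a limit: the article cannot be said to have chosen the less efficient model. The point remains because the stated model, read with predictions about reductions, leads most naturally to the interaction test, and a specific better model is available at no cost.

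A reader might also infer that the trial is underpowered. The document does not support that. It gives no r, and above about 0.5 the free-baseline model meets or exceeds the planned power. Short recall windows (14 days) and an index admission for trauma make a lower r conceivable, but no figure in the document establishes it. If the SDs differ between baseline and 6 months, the figures shift.

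The SD scale is also open. The wording favours the SD of weekly consumption, but if the 0.50 SD were the SD of change, the planned power would stand at any r.

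**Conclusion.** The point holds as an improvement to the primary analysis and as a mismatch between analysis and sample size on the natural reading. It is not a demonstrated shortfall in power. With 77 baselines and 62 follow-ups per arm, equal variances and the 0.50 SD on the weekly-consumption scale, the free-baseline model loses little against 0.80 just below r = 0.5, about 5 points at r = 0.4 and about 12 at r = 0.3. A common baseline mean keeps power at about 0.80 or higher for any r from 0 upwards. It is more precise than the free-baseline model for every r from 0 up to, but not including, 1. Assessment before allocation justifies the constraint.

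**What to change.** Specify the primary model as a linear mixed model with a common baseline mean for both conditions (constrained longitudinal model, unstructured covariance), and name the 6-month between-condition difference as the tested contrast. This keeps all randomised participants in the analysis, as the Analysis section intends. ANCOVA on completers alone has similar precision but would drop those without follow-up, so it is not an equivalent substitute here.

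In Sample size, state the assumed correlation and whether the 0.50 SD refers to weekly consumption or to its change. In Analysis, reconcile the count of two occasions with the three times listed.

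The cost is a few lines of wording, with no added participants, visits or data.

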## Feasibility

A total of more than 250 patients are admitted to the Royal Darwin Hospital maxillofacial unit each year. We anticipate that 62% of these inpatients will fulfil eligibility criteria for inclusion and that 77 patients per year will be eligible for randomisation over the 12-month recruitment period.

In order to minimise drop out we will undertake the following actions:

•  Obtaining at least 3 means of contacting participants at recruitment (Telephone number of participant, telephone number their carers -family member and participants address);

•  Following up by phone to update contacts and residential details every month;

•  Liaising with the surgical team to link follow-up assessments with client outpatient visits.

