**Methods and design:**

The study is a randomised controlled trial with 6 months of follow-up, to examine the effectiveness of a brief and culturally adapted intervention in improving outcomes for trauma patients with at-risk drinking admitted to the Royal Darwin Hospital maxillofacial surgery unit. Potential participants are identified using AUDIT-C questionnaire. Eligible participants are randomised to either Motivational Care Planning (MCP) or Treatment as Usual (TAU). The outcome measures will include quantity and frequency of alcohol and other substance use by Timeline Followback. The recruitment target is 154 participants, which with 20% dropout, is hoped to provide 124 people receiving treatment and follow-up.

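### The stated rate (77 a year) and 12-month recruitment period give at most 77 patients, half of the 154 target, so rate, period and target cannot all be right

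*Protocol article*

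**What the plan says.** The Sample size section of the protocol article plans for "a differential reduction in alcohol consumption of 0.50 SD in weekly alcohol consumption" and continues: "Setting the power at 0.80 and alpha at 0.05, 62 participants are required in each condition". It then allows for 20% attrition, "deriving a target baseline sample of 154". The Abstract (Methods and design) agrees: "The recruitment target is 154 participants", of whom 124 are hoped to complete treatment and follow-up.

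The Feasibility section puts annual admissions to the maxillofacial unit at more than 250. It then says "We anticipate that 62% of these inpatients will fulfil eligibility criteria for inclusion" and, in the same sentence, that "77 patients per year will be eligible for randomisation over the 12-month recruitment period".

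Only one hospital is named as a source of patients (Recruitment; Inclusion/exclusion criteria), and no longer recruitment period appears anywhere. The 12 months mentioned under Follow up assessment is the limit for tracing participants for follow-up, not a recruitment period.

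**The concern.** The article states a rate, a duration and a target, and the first two multiplied together give half of the third. This is not a detail left to a fuller document, because all three figures are printed and they disagree.

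The 77 is also a ceiling. It counts patients eligible for randomisation, so any loss between that point and allocation lowers the number randomised.

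The recruitment period matters because staffing, funding and the date of last follow-up depend on it. The Sample size section treats 0.50 SD as the smallest difference of clinical interest. A trial that stopped after the stated period at the stated rate would have about an even chance of missing a true difference of that size, and a null result would say little.

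**Working it through.** **Inputs.** Effect 0.50 SD, power 0.80, alpha 0.05, 62 per arm, 20% attrition and target 154 (Sample size). Admissions above 250 a year, 62% meeting criteria, 77 a year eligible for randomisation, 12 months (Feasibility). Allocation is taken as about 1:1, from the balanced randomisation under Procedure. The article does not say whether alpha is one- or two-sided.

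**1. The plan's own sample size.**
- Two-sided, normal approximation: n per arm = 2 × (1.96 + 0.8416)² / 0.50² = 62.8, so 63. The t-test gives 64 and the plan gives 62. A one-sided test would need only 50 by the normal approximation, so two-sided is inferred.
- Power at 62 per arm: 0.795 (normal) or 0.789 (t-test), against 0.80 stated.
- Attrition: 124 / 0.80 = 155, against 154 stated. In reverse, 154 × 0.80 = 123.2.

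The sample size reproduces within rounding. The fault is not there.

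**2. Supply on the stated rate and period.**
- 77 per year × 1 year = 77, and 77 / 154 = 50%.
- Time to reach 154 at that rate: 154 / 77 = 2.0 years, or 24 months.

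**3. Whether the 62% figure closes the gap.**
- 250 × 0.62 = 155 a year meeting criteria.
- Uptake needed for 154 in 12 months: 154 / 155 = 99%. Because admissions are given as more than 250, this is an upper bound.
- Admissions needed at lower uptake (assumed values): at 90%, 154 / (0.62 × 0.90) = 276 a year; at 70%, 154 / (0.62 × 0.70) = 355 a year.
- The article's own figure for those eligible for randomisation, 77, is 77 / 155 = 49.7% of those meeting criteria.

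**4. Power if 77 are randomised and recruitment closes at 12 months.**
- 77 × 0.80 = 61.6 analysed, 30.8 per arm (about 31).
- Normal approximation: 0.50 × √(30.8 / 2) − 1.96 = 0.00, so power is 0.50. The t-test at 31 per arm gives 0.49.
- With no attrition (38.5 per arm): 0.59 (normal) or 0.58 (t-test).
- Difference detectable with 80% power: 2.8016 × √(2 / 30.8) = 0.71 SD. The t-test at 31 per arm gives 0.72 SD.

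**5. Sensitivity to baseline adjustment.** If the 0.50 SD refers to the raw outcome SD and the baseline to 6-month correlation is r, the residual SD shrinks by √(1 − r²). With 30.8 per arm:

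| r (assumed) | Power |
|---|---|
| none used | 0.50 |
| 0.5 | 0.62 |
| 0.7 | 0.78 |
| 0.75 | 0.84 |

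The article gives no correlation, and its 62 per arm uses none.

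**The case against.** A reader might infer that the trial is underpowered by design and that 0.80 power is out of reach. The article does not support that. The target of 154 is fixed in two places, and nothing says that recruitment closes short of it. The loss of power follows only if the 77 and the 12 months both hold and recruitment then stops. The planned mixed model could also recover some power, as step 5 shows, although the article gives no basis for counting on it.

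A reader might also infer that 155 and 77 are two incompatible counts of the same thing. They need not be. The first is described as meeting the inclusion criteria and the second as eligible for randomisation, and Procedure places consent, screening and a full baseline assessment before allocation. A fall from 155 to 77 across those steps is coherent, even though the article does not explain it.

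Finally, 77 is exactly half of 154, which suggests a drafting slip: 77 may have been meant per condition, or the period may have been meant as 24 months. That is plausible, but the text says neither. The per-condition reading also brings back the need for near-complete uptake at 250 admissions. On either explanation, something printed in Feasibility has to be corrected.

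**Conclusion.** The point holds as an inconsistency. At 77 a year for 12 months, at most 77 patients are available against a target of 154, and nothing in the article reconciles the two. The 155 a year meeting criteria does not do so without uptake close to 100%, or admissions well above the 250 floor.

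The consequence for power is conditional. If recruitment ended at 12 months with 77 randomised and 20% were lost, power for 0.50 SD would be about 0.49 and the detectable difference at 80% power about 0.72 SD. This assumes a two-sided 0.05 test, equal arms and no gain from baseline adjustment. It is not a finding that the trial will be underpowered, and the sample-size calculation itself is sound. Which of the printed figures is wrong cannot be settled from the article.

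**What to change.** The sponsor should state which element of the Feasibility sentence is wrong: the 77, its description as a yearly count, or the 12 months. The paragraph should then give one chain: admissions per year, number meeting criteria, expected uptake, number randomised per year, and months needed to reach 154. If 77 a year is the total, the last figure is about 24 months. That is one possible reconciliation and the sponsor must confirm it.

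If 77 and 12 months both stand, the Sample size section and the Abstract should instead give the achievable sample (77 randomised, about 62 analysed) with its power or detectable difference. Any credit for baseline adjustment should come with the assumed correlation.

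The cost is a restatement of a few figures. If 154 is kept, neither the design nor the target changes. Whether the ethics approval or registry entry also needs amending cannot be judged here, since neither record is at hand and either may already carry the intended period.

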## Consent and culturally appropriate approach

Research officers will use pictorial and plain English information sheets, screening and intervention tools to assist understanding. Aboriginal and Torres Strait Islander participants will be offered communication support (interpreters, translators, assessed communication and inclusion of a support and cross-cultural family member or person of their choice). All information will be presented to participants by Indigenous researchers in a culturally appropriate manner, and written assessments will be administered orally in cases of limited literacy.

## Ethics and confidentiality

The study has been granted ethical approval by the Human Research Ethics Committee of Department of Health and Families and Menzies School of Health Research. The approval number is HREC 2010–1438. Electronic data is password-protected, and identifying data is kept on a separate database from outcome data, allowing de-identification at the end of data collection. Assessment data will be accessible only to the investigators and support team.

## Discussion

This project will introduce a practical approach to integrating brief interventions into the hospital setting, and has the potential to demonstrate significant benefits for at-risk drinkers with facial trauma. Findings from this project are expected to inform hospital-based treatment and secondary prevention of alcohol-related injury, not just in indigenous people in NT, but in other trauma treatment units throughout the world.
